## 11.3. Main Analysis

In this study, the primary analysis will focus on the average Time in Range (TIR) measured by CGM (Continuous Glucose Monitoring) up to the second postoperative day, which is the primary endpoint to be evaluated after patient enrollment is complete. Using analysis of covariance (ANCOVA), the adjusted mean difference in the primary endpoint between the two groups (intervention group - control group) will be calculated along with the 95% confidence interval and standard deviation. Additionally, as a reference, the p-value for the null hypothesis that the mean difference between the two groups is zero will be provided, along with the mean value (least-squares mean) and its 95% confidence interval and standard deviation for each group, including the results without adjusting for allocation factors. The average TIR up to the second postoperative day is defined as the proportion of time within the 48-hour period where blood glucose is within the therapeutic range of 70-180 mg/dL.

## 11.4. Sub-evaluation projects (efficacy).

For the following items, calculate the mean values and the corresponding 95% confidence intervals and standard deviations for each group and the intergroup difference (intervention group - control group). If necessary, calculate the p-values using Welch's t-test for comparisons between the two groups.

- Average TAR (Time Above Range) over the entire measurement period (Postoperative Day 1 to Day 8) measured by CGM
- Daily TAR up to Postoperative Day 8 measured by CGM
- Average AUC (Area Under the Curve) over the entire measurement period (Postoperative Day 1 to Day 8) measured by CGM
- Daily AUC up to Postoperative Day 8 measured by CGM
- Average TIR (Time in Range) over the entire measurement period (Postoperative Day 1 to Day 8) measured by CGM
- Daily TIR up to Postoperative Day 8 measured by CGM

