## 5.2. Randomization and Randomization Factors

After registering a case in the EDC system, the patient will be randomly assigned to one of the groups by the EDC system. The allocation factors are surgical time (≥ 560 min or < 560 min) and HbA1c value (HbA1c < 6.0 or 6.1-6.4), which are factors of particular concern that may impact the primary outcome. The minimization method will be used to ensure that significant imbalances do not occur. Details of the allocation factors will remain blinded to the patients.

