### 6.1.3. Blood Glucose Management

In this study, after the patient returns to the ward immediately post-surgery, the sub-investigator will attach the FreeStyle Libre Pro to the outer upper arm of the patient and begin continuous glucose monitoring (CGM). The sub-investigator will remove the FreeStyle Libre Pro from the patient on postoperative day 9. In addition, from the time the patient returns to the ward, blood glucose will be routinely measured 4 times a day using either blood gas analysis or the Dexter system.

Rescue treatments for hyperglycemia and hypoglycemia will be managed based on the blood glucose values obtained from the routine measurements via blood gas analysis or the Dexter system. Blood glucose information obtained from the FreeStyle Libre Pro will not be used as a reference for determining whether to perform rescue treatments for hyperglycemia or hypoglycemia.

Rescue treatments for hyperglycemia and hypoglycemia will be conducted as described below. However, rescue treatment for blood glucose levels between 201-299 mg/dL will not be permitted until the second postoperative day.

Criteria for rescue treatment for postoperative hyperglycemia and hypoglycemia

| Blood glucose (mg/dL) | | season | Fast-acting insulin | 50% Dextrose |
| --- | --- | --- | --- | --- |
| Hyperglycemia | 201 or more ~ 249 or less | Up to postoperative day 2 | None | - |
|  |  | From the 3rd postoperative day onwards | 2 Units | - |
|  | 250 or more ~ 299 or less | Up to postoperative day 2 | None | - |
|  |  | From the 3rd postoperative day onwards | 4 Units | - |
|  | 300 or more ~ 349 or less | Postoperative day 1 and beyond | 6 Units | - |
|  | 350 or more ~ 399 or less | Postoperative day 1 and beyond | 8 Units | - |
|  | 400 or more | Postoperative day 1 and beyond | 10 Units | - |
| hypoglycemia | 69 or less | Postoperative day 1 and beyond | - | 20mL |

<Rationale for rescue treatment for hyperglycemia and hypoglycemia>

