## 8.2. Evaluation items on the day of surgery

1. Surgery Information
2. Allocation
3. FreeStyle Libre Pro attachement
4. 24-hour continuous glucose monitoring
5. Confirmation of Survival

## 8.3. Evaluation Items on Postoperative Day 1

1. Conformation of FreeStyle Libre Pro Continues
2. 24-hour continuous glucose monitoring
3. Blood glucose measurement 4 times a day with blood gas
4. Continuous administration of 400 mL of enteral nutrition (Meiji Main and Glucerna®-REX)
5. If necessary, the rescue of insulin for hyperglycemia and hypoglycemia
6. Presence or absence of postoperative infectious complications
7. Presence or absence of other complications
8. Adverse events
9. Confirmation of survival or death

## 8.4. Evaluation Items on Postoperative Days 2 to 3

1. Conformation of FreeStyle Libre Pro Continues
2. 24-hour continuous glucose monitoring
3. Blood glucose measurement 4 times a day with blood gas
4. Continuous administration of enteral nutrition (Meiji Main and Glucerna-REX ®) (postoperative day 2; 800 mL, postoperative day 3: 1200 mL)
5. If necessary, the rescue of insulin for hyperglycemia and hypoglycemia
6. Presence or absence of postoperative infectious complications
7. Presence or absence of other complications
8. Adverse events
9. Confirmation of survival or death

## 8.5. Evaluation Items on Postoperative Days 4 to 8

1. Conformation of FreeStyle Libre Pro Continues
2. 24-hour continuous glucose monitoring
3. Blood glucose measurement 4 times a day with dexter
4. Continuous administration of enteral nutrition (Meiji Main and Glucerna-REX ®) (postoperatively 4 days or later; 1600 mL)

Dosage may be changed or enteral nutrition may be changed depending on the patient's condition (e.g., adverse events) (see 6.2.3.)

1. If necessary, the rescue of insulin for hyperglycemia and hypoglycemia
2. Presence or absence of postoperative infectious complications
3. Presence or absence of other complications
4. Adverse events
5. Confirmation of survival or death

## 8.6. Evaluation Items on Postoperative Day 9

1. Remove the FreeStyle Libre Pro. (Postoperative 1~Collection of blood glucose data on day 8)
2. Enteral nutrition: Change of administration to Heinegel (change timing can be changed depending on the patient's condition)

However, if Meiji Main and Glucerna-REX ® are still administered after the 9th postoperative day, until the end of administration

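### Section 11.4 estimates the secondary CGM endpoints without the minimisation factors, so their intervals are too wide to the extent that those factors are prognostic

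*Protocol*

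**What the plan says.** Section 5.2 names the two factors, "The allocation factors are surgical time (≥ 560 min or < 560 min) and HbA1c value (HbA1c < 6.0 or 6.1-6.4", and describes them as ones "which are factors of particular concern that may impact the primary outcome". On the method it says: "The minimization method will be used to ensure that significant imbalances do not occur".

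Section 11.3 follows from this for the primary endpoint: "Using analysis of covariance (ANCOVA), the adjusted mean difference in the primary endpoint between the two groups (intervention group - control group) will be calculated". Alongside the p-value and the group means it asks for supporting results, "including the results without adjusting for allocation factors". The section gives no explicit covariate list. That phrase is its only pointer to what the ANCOVA contains.

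Section 11.4 covers six CGM endpoints: TIR, TAR and AUC, each as an average over postoperative days 1 to 8 and day by day. It asks for group means and the between-group difference with 95% intervals and names no covariate. It then says: "If necessary, calculate the p-values using Welch's t-test for comparisons between the two groups". The condition applies to the p-values only. The differences and intervals are planned in any case.

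**The concern.** When allocation is balanced on factors that predict the outcome, the arms are more alike than under simple randomisation. The true variance of the difference in means is then smaller than the ordinary two-sample formula assumes. An analysis that leaves the factors out keeps their variance in the standard error, so its nominal 95% interval covers more often than 95%.

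The protocol accepts this logic in section 11.3 and drops it in section 11.4. The effect shows most clearly in daily TIR on postoperative days 1 and 2, which fall in the period of the primary endpoint. Closely related data would have an adjusted headline estimate in one section and an unadjusted one in the next.

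This matters because the trial is built on precision. Sections 2.4.2 and 11.6 justify the sample size only by the width of the confidence interval, and section 2.6 says that the results are to inform later confirmatory trials.

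**Working it through.** **Inputs.** SD 8.5%, 48 analysable patients and a target of about ±5% (sections 2.4.2 and 11.6); equal arms, so 24 each; two-sided 95% intervals (section 11.8); two binary factors (section 5.2). The protocol does not say how much of the outcome variance the factors explain. That share, R², is assumed below.

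**The protocol's own figure.** Half-width = quantile × SD × √(1/24 + 1/24).
- Standard error: 8.5 × √(2/24) = 2.454.
- Normal quantile: 1.960 × 2.454 = 4.81.
- t quantile, 46 df: 2.013 × 2.454 = 4.94.

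Both round to ±5, so the stated precision is that of an unadjusted two-sample comparison. It reproduces only if 8.5% is the SD between patients. Read literally as the SD of the difference between groups, it gives 1.960 × 8.5/√48 = 2.40 or 1.960 × 8.5/√24 = 3.40.

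**With the two factors in the model.** Half-width = t(44 df) × 2.454 × √(1 − R²), with t = 2.015.
- R² = 0: 4.95, so no gain and a trivial loss.
- R² = 0.1: 2.015 × 2.454 × 0.949 = 4.69.
- R² = 0.2: 2.015 × 2.454 × 0.894 = 4.42.
- R² = 0.3: 2.015 × 2.454 × 0.837 = 4.14.

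**Coverage by simulation.** The setting was 48 patients, two equally common binary factors, minimisation with a biased coin of 0.8 (assumed) and no treatment effect. Each R² had four sets of 3,000 runs, which differed in the strength of a further predictor used by neither analysis. Ranges are over the four sets. The Monte Carlo standard error of a coverage is √(0.95 × 0.05/3000) = 0.4 percentage points.

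| Assumed R² | Welch half-width | Welch coverage | Adjusted half-width | Adjusted coverage |
| --- | --- | --- | --- | --- |
| 0 | 4.91–4.93 | 94.2–95.4% | 4.92–4.94 | 94.2–95.3% |
| 0.1 | 4.92–4.93 | 95.4–95.7% | 4.67–4.68 | 94.2–95.0% |
| 0.2 | 4.91–4.94 | 96.5–97.1% | 4.39–4.41 | 94.4–95.0% |
| 0.3 | 4.94 | 97.4–98.0% | 4.12–4.14 | 94.5–95.5% |

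The Welch intervals stay the same width however prognostic the factors are, and they over-cover as R² rises. The adjusted intervals narrow and stay close to 95%.

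**Scope.** The 8.5% is a figure for TIR. The protocol gives no SD for TAR or AUC. The relative narrowing, √0.9 = 0.95 and √0.8 = 0.89, would apply to them at the same R².

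**The case against.** The Welch comparison is valid. It errs on the safe side, the endpoints are secondary and without multiplicity adjustment, and the trial is meant to generate hypotheses. All of that stands, and it limits the point to efficiency and consistency. Welch also allows unequal variances, whereas ordinary ANCOVA does not, and TIR, TAR and AUC above a threshold are bounded measures. That is a fair cost, but it already applies to the primary analysis, and robust standard errors deal with the variance part.

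It can also be said that details belong to the separate analysis plan. Section 11.4, however, states a method. Section 11 requires reasons for any departure from the planned analyses, so a plan that simply follows the protocol carries the weakness over. The mismatch with the primary is softened because section 11.3 already gives unadjusted primary results as a reference.

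A reader might go further and infer that the primary ANCOVA leaves out a pre-formula glucose value that exists for every patient, and so gives away precision worth a known number of patients. The protocol does not support this:
- Section 11.3 lists no covariates, so an omission cannot be shown.
- Sections 6.1.3 and 8.2 and the calendar in 8.9 start CGM on the day of surgery, but sections 2.3.3 and 8.6 speak of data for days 1 to 8.
- Section 6.1.3 has glucose checked "from the time the patient returns to the ward, blood glucose will be routinely measured 4 times a day", but 8.2 lists no such check and 8.9 marks it only from day 1.
- Section 11.3 gives no start for its 48-hour window. If it opens when the sensor is attached, day-0 glucose is part of the outcome and cannot be a baseline.
- Any gain depends on a partial correlation, beyond the allocation factors, that the protocol does not give. Applying an assumed simple correlation to the unadjusted ±4.94 does not answer that.

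**Conclusion.** The point holds for section 11.4. The secondary CGM endpoints are estimated without factors that the protocol itself considers prognostic and uses for allocation, while the primary endpoint is analysed by ANCOVA. The consequence is intervals that are too wide, by about 5% if the factors explain 10% of the variance (±4.9 against ±4.7) and about 11% if they explain 20% (±4.9 against ±4.4). There is no consequence if they explain none. The figures rest on the assumed R², on 8.5% as a between-patient SD and on 24 patients per arm.

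Two readings go too far. Bias or excess false positives would be the wrong charge, since the Welch test becomes conservative here. A claim that the primary analysis wastes a known amount of precision for want of a day-0 glucose covariate is not supported either. The change is worth making because it is cheap and brings the two sections into line. No planned analysis is invalid without it.

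**What to change.** In section 11.4, use the allocation-factor ANCOVA of section 11.3 for TIR, TAR and AUC, both the day 1 to 8 averages and the daily values, and report adjusted differences with 95% intervals. Keep the unadjusted means and Welch results as reference, as section 11.3 already does for the primary endpoint. State in 11.3 which covariates the ANCOVA contains. Enter each factor at the level recorded at allocation; section 5.2 as written places an HbA1c of exactly 6.0 in neither category, and this should be settled too. The cost is a few words, about two degrees of freedom and a common-variance assumption, which robust standard errors can relax.

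Optionally, add a pre-formula glucose covariate to section 11.3. This should wait until sections 2.3.3, 6.1.3, 8.2, 8.6 and 8.9 agree on what is recorded on the day of surgery and 11.3 fixes the start of its 48 hours. The covariate needs a fixed window wholly outside that period. Its gain is unknown, so no sample-size equivalent should be claimed for it.

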## 11.5. Sub-secondary evaluation (safety)

For the following items, calculate the frequency, percentage, and corresponding 95% confidence interval for each group. The 95% confidence intervals should be calculated using Clopper & Pearson's exact confidence interval method. If necessary, perform a chi-squared test to compute the p-values for comparisons between the two groups.

For adverse events, calculate the number of cases, number of occurrences, proportion of cases, and their 95% confidence intervals using Clopper & Pearson's exact method. The analysis should also include a breakdown by grade and causal relationship. Additionally, create a comprehensive list of all adverse events.

- Incidence rate of infectious complications during the hospitalization period
- Incidence rate of infectious complications within 30 days postoperatively
- Incidence rate of all complications during the hospitalization period
- Incidence rate of adverse events
- Number of cases requiring glycemic control intervention for hyperglycemia (≥ 300 mg/dL)
- Number of cases in which enteral nutrition was modified after postoperative Day 3
- Number of cases requiring a reduction of more than 50% of enteral nutrition compared to the previous day after postoperative Day 3

For the following items, calculate the median and interquartile range (IQR) for each group at all measurement points. Also, calculate the median and IQR for changes from baseline values (pre-registration measurements). If necessary, also calculate the mean and standard deviation, as well as p-values using the Wilcoxon test.

- Nutritional indicators during the hospitalization period (serum albumin levels, prealbumin levels, and total protein levels)

)

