In a retrospective study conducted prior to this trial, we examined the relationship between postoperative blood glucose levels and infectious complications in esophageal cancer patients. We reported that not only diabetic patients but also non-diabetic patients who experience postoperative hyperglycemia are at an increased risk of infectious complications. Moreover, surgical stress was found to contribute to postoperative hyperglycemia [4]. In our study, patients with an average blood glucose level of 200 mg/dL or higher on postoperative day 1 had a significantly higher incidence of infectious complications compared to those with an average blood glucose level below 200 mg/dL (hyperglycemic group: 39.3% vs. non-hyperglycemic group: 25.6%, P = 0.0068). Subgroup analysis showed that this trend was observed not only in diabetic patients (hyperglycemic group: 39.3% vs. non-hyperglycemic group: 25.6%, P = 0.0068) but also markedly in non-diabetic patients (hyperglycemic group: 42.9% vs. non-hyperglycemic group: 25.2%, P = 0.0022). Furthermore, multivariate analysis of subgroups revealed that an average blood glucose level of 200 mg/dL on postoperative days 1, 2, and 4 was an independent risk factor for infectious complications in non-diabetic patients [multivariate hazard ratio for hyperglycemic group compared to non-hyperglycemic group: postoperative day 1: 1.94, postoperative day 2: 3.68, postoperative day 4: 3.07].

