## 11.8. Intentional level and multiplicity

The significance level for all analyses in this trial is 5% two-tailed, and the confidence factor for the confidence interval is 95% two-tailed. Neither efficacy nor safety evaluation will be adjusted for multiplicity between endpoints or time points.

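### Section 11.5 compares the arms on binary complication and safety endpoints only by an optional chi-squared p-value, and gives no risk difference with a confidence interval as 11.3 and 11.4 do for the glucose endpoints

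*Protocol*

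**What the plan says.** Protocol 11.5 covers seven binary items: infectious complications in hospital and within 30 days, all complications in hospital, adverse events, intervention for glucose of 300 mg/dL or more, change of formula, and reduction of feed by more than half. For these the analyst is to "calculate the frequency, percentage, and corresponding 95% confidence interval for each group", and "The 95% confidence intervals should be calculated using Clopper & Pearson's exact confidence interval method". The between-arm step is one sentence: "If necessary, perform a chi-squared test to compute the p-values for comparisons between the two groups". Adverse events are also counted by case and occurrence, broken down by grade and causal relationship, and listed in full. No risk difference, ratio or between-arm interval is named.

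The neighbouring sections work differently. For the CGM secondary endpoints, 11.4 asks for means with "95% confidence intervals and standard deviations for each group and the intergroup difference (intervention group - control group"). For the primary endpoint, 11.3 asks for the adjusted mean difference with its 95% interval and offers the p-value only for reference.

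Section 11.8 adds "The significance level for all analyses in this trial is 5% two-tailed", and "Neither efficacy nor safety evaluation will be adjusted for multiplicity between endpoints or time points".

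**The concern.** The trial is built on estimation. Sections 2.4.2 and 11.6 justify 50 patients by the width of a confidence interval, not by a test, and section 2.6 says the findings will generate hypotheses for confirmatory trials. Infectious complications are the clinical rationale in section 2.1 and head the list of secondary endpoints. Yet they and the other binary endpoints are the ones for which the plan names no estimate of the between-arm effect and no statement of its precision.

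A p-value from about 24 patients per arm says little about which differences remain plausible. Two one-sample intervals do not say it either, because the uncertainty of a difference cannot be read from whether they overlap. A team planning the confirmatory trial needs the difference and its interval, and the planned tables would not show them.

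**Working it through.** **Inputs.** 48 patients, so 24 per arm, and SD 8.5% (2.4.2, 11.6). All treated cases for safety, so up to 25 per arm (11.1, 11.6). Two-sided 5% level and 95% intervals (11.8). Background infectious complication rate 127/430 = 29.5%, about 30% (2.1).

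**1. The plan's own precision figure.** Half-width = quantile × 8.5 × √(2/24). With 1.96 this is 4.81 points; with the t quantile on 46 degrees of freedom, 4.94 points. The stated ±5% is reproduced if 8.5% is read as the per-patient SD. No matching figure is given for any binary endpoint.

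**2. What the p-value and the difference interval each show, 24 per arm.** The Wilson limits for x/n have centre (p + z²/2n)/(1 + z²/n) and half-width z√(p(1-p)/n + z²/4n²)/(1 + z²/n). Newcombe's limits for d = p1 - p2 are d - √((p1-l1)² + (u2-p2)²) and d + √((u1-p1)² + (p2-l2)²).

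- *7 vs 7.* p = 0.2917 in both arms, Wilson limits 0.149 to 0.492. d = 0; margin = √(0.1425² + 0.2000²) = 0.246. Interval -24.6 to +24.6 points; chi-squared p = 1.0.
- *10 vs 6.* p1 = 0.4167 (Wilson 0.245 to 0.612), p2 = 0.2500 (0.120 to 0.449), d = +16.7 points. Lower margin √(0.1720² + 0.1990²) = 0.263; upper margin √(0.1950² + 0.1300²) = 0.234. Interval -9.6 to +40.1 points. The uncorrected chi-squared is 0.1667²/((1/3)(2/3)(2/24)) = 1.5, p = 0.22.
- *12 vs 7.* d = +20.8 points, interval -6.5 to +44.2 points, p = 0.14.

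**3. What 11.5 would print for 10 vs 6.** Clopper-Pearson intervals of 22% to 63% and 10% to 47%, with p = 0.22 if the test is run. The range of -10 to +40 points appears nowhere.

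**4. Illustration of the p-value's behaviour.** All 25 × 25 outcome tables at 24 per arm were weighted by their binomial probabilities, and those with p < 0.05 summed. The alternatives are assumptions, since the protocol sets none.

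| True rates | Non-significant, uncorrected | Non-significant, continuity-corrected |
|---|---|---|
| 30% vs 45% | 80% | 88% |
| 30% vs 50% | 69% | 79% |
| 30% vs 60% | 41% | 53% |

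With 25 per arm the two extremes become 38% (30% vs 60%, uncorrected) and 86.5% (30% vs 45%, corrected).

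**The case against.** **It belongs in the SAP.** Section 11 leaves details to a separate plan that is not shown, and the choice of interval for a difference is ordinary SAP content. This would carry weight if 11.5 were silent. It is not: it names the summary, the interval method and the test, and stops short of the quantity that 11.3 and 11.4 ask for. If the SAP already adds the difference and its interval, the point is met.

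**Nothing is lost.** Counts per arm will be reported, so any reader can work out the risk difference and its interval. That is true, and it keeps the point modest. A reader might infer that a non-significant p-value would be the only comparative safety information. The document does not support that: rates with exact intervals, grade and causality breakdowns and a full listing are all planned, and the test is optional. What is missing is the interval for the difference.

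**The protocol never treats p > 0.05 as evidence of safety.** Correct. A reader might infer an intended claim of similar complication rates, but no equivalence or safety conclusion is stated.

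**Power figures do not measure the defect.** This also stands. It is tempting to take the retrospective contrast in section 2.1, "markedly in non-diabetic patients (hyperglycemic group: 42.9% vs. non-hyperglycemic group: 25.2%, P = 0.0022"), and say that a relevant harm would be missed 74% of the time (exact power 25.9% at 24 per arm, uncorrected). The arithmetic is right but the label is not. That contrast compares patients by glucose level, not by formula, and under the trial's hypothesis it would point to a benefit of the intervention. Low power follows from 50 patients, a number that 2.4.2 openly attributes to feasibility, and a difference interval does not change it.

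**Conclusion.** The point holds as one of estimation and reporting. For its binary endpoints 11.5 fixes a weaker between-arm comparison than 11.3 and 11.4 fix for the continuous ones, and this sits badly with a trial sized on precision. At 24 per arm and event rates near 30%, the unreported uncertainty is about ±25 points around no difference, and -10 to +40 points around an observed excess of 17.

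These figures rest on 24 evaluable patients per arm (up to 25 in the safety set, which changes little), on illustrative event counts near the site's own rate, and on Newcombe's method. The 41% to 88% chance of a non-significant result at 24 per arm is illustration only, because the protocol defines no relevant harm.

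The primary analysis is untouched, and no statement in the protocol is shown to be false.

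**What to change.** In 11.5, for each binary endpoint, make the between-group comparison the risk difference (intervention minus control) with a two-sided 95% confidence interval by Newcombe or Miettinen-Nurminen, and name the method. For adverse events, apply it to the proportion of patients with an event. Keep the Clopper-Pearson intervals as the description of each arm. If a chi-squared p-value is shown, label it as reference only, as 11.3 does. The intervals would be unadjusted for multiplicity, in line with 11.8.

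The cost is one or two sentences in 11.5 or the SAP and a few table columns, with no new data, patients or visits. The only downside is that the intervals will be visibly wide. The change does not raise power.
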